**Methods:**

This is a single-center, single-blind, split-mouth randomized controlled trial conducted at the Orthodontic Clinic, International Islamic University Malaysia. Eligible participants are patients aged 15 years and older, medically fit with Basic Periodontal Examination scores of 0‐2, requiring full fixed appliance treatment with bilateral premolar extractions and no prior orthodontic treatment. Those with craniofacial deformities, systemic illness, or disability affecting oral hygiene compliance are excluded. Each participant’s oral cavity is randomly allocated using a minimization method, so that one side receives a passive 0.010-inch stainless-steel laceback from the first molar hook to the canine bracket, while the contralateral side receives identical standard fixed appliance treatment (McLaughlin, Bennett, and Trevisi prescription brackets, 0.014-inch superelastic nickel-titanium archwires, and elastomeric modules) without laceback. Outcomes are assessed at baseline (T0), 4 weeks (T1), and 8 weeks (T2) after laceback placement. The primary outcome is the orthodontic plaque index. Secondary outcomes include archwire and laceback complication frequencies and pain assessed by visual analog scale area under the curve. A total of 38 participants provided 85% power to detect a 1-unit orthodontic plaque index difference (*α*=.05). Mixed-model repeated-measures analysis is applied to plaque scores; paired parametric or nonparametric tests to other outcomes. Plaque and archwire assessors are blinded to treatment allocation.

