Currently, despite equivocal evidence regarding the effectiveness of laceback in controlling forward tipping of anterior teeth and risk of posterior anchorage loss, laceback is still routinely used by clinicians in selected cases. In view of the paucity of data on oral hygiene status and patient-reported outcomes following laceback usage, this research aims to evaluate the clinical and PROs of laceback usage during the alignment phase of orthodontic fixed appliance treatment. The specific objectives are to assess the effect of laceback on a patient’s oral hygiene, to investigate the effect of laceback on the frequency of archwire complications, to determine the frequency of laceback complications, and to study the effect of laceback on pain. It is hoped that the results obtained may identify treatments that are both clinically effective and acceptable to patients, as well as provide supportive evidence for clinicians to judiciously weigh the risks and benefits of using lacebacks. The null hypothesis is that there will be no statistically significant difference in clinical and PROs between laceback (intervention) and no laceback (control) groups during the alignment phase of orthodontic fixed appliance treatment.

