## Methods

### Study Design

This is a single-center, single-blind, split-mouth randomized controlled trial with a 1:1 allocation ratio for the 2 groups (left and right sides of the oral cavity). In this study, either the left or right side of each participant’s oral cavity is randomly assigned to receive a laceback, while the contralateral side serves as the control (no laceback). The study is aimed to fulfill as many items as possible in the CONSORT (Consolidated Standards of Reporting Trials) 2025 checklist for reporting randomized controlled trials, and the SPIRIT (Standard Protocol Items: Recommendations for Interventional Trials) 2025 checklist for preparing protocols of randomized controlled trials [18,19].

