**Orthodontic factors**
Full upper and lower arch orthodontic fixed appliance.Extraction of bilateral upper and lower permanent first or second premolars at least 2 weeks before bond-up.No previous orthodontic treatment.
**
*Exclusion criteria*
**
Craniofacial deformities.Mental or physical disability leading to impaired manual dexterity and difficulty comprehending and following oral hygiene instructions.Underlying chronic medical illness, oral diseases.
**
*Withdrawal criteria*
**
Participants are free to withdraw anytime during the period of study. Reasons for withdrawal will be noted down. Possible criteria of withdrawal include:Serious adverse events arising from laceback, which is very unlikely as it has not been reported in literature.Participant not following study procedures.Participant unwilling to continue orthodontic treatment.

An intention-to-treat analysis is used, whereby data from all participants is analyzed irrespective of any subsequent withdrawal or protocol deviation to ensure that the results will reflect the effects of laceback in a real-world setting, while maintaining the study power because no participants are omitted from the analysis [20,21]. Repeated measures data for plaque score and pain score will be analyzed using a mixed model for repeated measures (MMRM), which accounts for within-participant correlation and handles missing data without formal imputation under the missing at random assumption [22].

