#### Interventions Common to Both Groups

The participants of this research undergo active orthodontic treatment at the postgraduate orthodontic clinic. The same bracket system, Master Series, 0.022-inch slot, MBT prescription metal brackets (American Orthodontics), and initial archwire (0.014-inch Euroform Super Elastic Nickel Titanium; Ortho-Care) are used for all participants. All brackets are bonded using the same standardized protocol, which involves 37% phosphoric acid etchant (Acid Etchant; American Orthodontics), light-cured adhesive primer (reliaBond Light-Cure Bonding Adhesive 5th Generation; Advanced Healthcare Ltd), and orthodontic composite resin (BracePaste Adhesive; American Orthodontics), following the manufacturer’s instructions. Extractions of all first or second premolars are done at least 2 weeks before the appointment for bond-up of orthodontic fixed appliances, so as to minimize pain arising from the extraction site that may confound the pain assessment. Archwires are ligated using elastomeric modules (EKSEN). The ends of the archwires are cut flush to the molar tubes and not cinched. Bite planes, intermaxillary elastics, headgear, or any auxiliaries are not used during the study period. The principal investigator delivers oral hygiene instructions, dietary instructions, and braces care instructions verbally with demonstration on a model using a standard script. An educational video on post-bond-up instructions is created and sent to the participants’ mobile devices for viewing. A patient information leaflet on brace care is also provided. All participants are supplied with a fluoridated toothpaste (Colgate Maximum Cavity Protection Fresh Cool Mint Toothpaste; Colgate-Palmolive Company) and a soft-bristle toothbrush (Colgate Zig Zag Toothbrush; Colgate-Palmolive Company). They are requested not to use any additional oral hygiene aids throughout the duration of the research. Participants undergo one round of scaling before lacebacks are placed during T_0_. Thereafter, they are informed not to go for professional teeth cleaning during the study period. Participants are reminded to check their braces for any dislodgement and breakage twice daily (morning and evening). If there are any orthodontic emergencies, participants are advised to call the clinic for an emergency appointment as soon as possible. Participants are also advised not to brush their teeth 2 hours before their appointments.

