### Intended Statistical Analysis

Statistical analysis is conducted using IBM SPSS Statistics (version 31). Descriptive statistics are used to report participant demographics, baseline characteristics, and frequency of laceback complications. To assess whether the data are normally distributed, interpreting the shape of the histogram and the Shapiro-Wilk test are used. Intra- and interrater reliability for plaque score assessment are measured using Cohen kappa. The threshold for good inter- and intrarater reliability is set to be more than 0.8.

Repeated outcome measurements of plaque scores will be analyzed using a mixed model for repeated measures. The model includes treatment group, time, and treatment-by-time interaction as fixed effects, with participant included as a random effect. A mixed model for repeated measures allows inclusion of participants with incomplete follow-up data without requiring formal imputation, assuming data are missing at random. If the data are not normally distributed, plaque scores over time (T_0_, T_1_, and T_2_) will be compared using the Friedman test.

From the pain diary gathered, the pain scores are plotted against time to allow calculation of area under the curve (AUC) using the trapezoidal rule [34]. Pain AUC will be calculated between T_0_ and T_1_ and T_1_ and T_2_. The mean pain AUC for laceback and no laceback sides will be calculated by averaging pain AUC values between T_0_ and T_1_ and between T_1_ and T_2_. To compare differences in mean pain AUC of laceback and no laceback groups, a paired *t* test is used if data are normally distributed. If the normality assumption is violated, the Wilcoxon signed-rank test is applied instead.

The mean frequency of archwire complications is recorded by summing up the number of complications that happen throughout the study period from T_0_ to T_2_. To compare differences in the mean frequency of archwire complications between the laceback and no laceback groups, a paired *t* test is used if data are normally distributed. The mean frequency of laceback complications and the number and percentage of participants with at least 2 laceback complications are also reported. The value of *P*<.05 is considered statistically significant.

Sensitivity analysis will be conducted by comparing the results of intention-to-treat and per-protocol analyses. If both analyses yield similar results, this demonstrates the robustness and validity of the study’s conclusions.

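### The fallback for non-normal plaque scores is a Friedman test across visits, which tests change over time and not laceback against no laceback

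*Protocol article*

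**What the plan says.** The Abstract sets the endpoint: "The primary outcome is the orthodontic plaque index". The Introduction sets the comparison: "The null hypothesis is that there will be no statistically significant difference in clinical and PROs between laceback (intervention) and no laceback (control) groups". Study Design describes a "split-mouth randomized controlled trial with a 1:1 allocation ratio for the 2 groups (left and right sides of the oral cavity").

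Intended Statistical Analysis analyses plaque with a mixed model for repeated measures: "The model includes treatment group, time, and treatment-by-time interaction as fixed effects, with participant included as a random effect". It then adds the contingency: "If the data are not normally distributed, plaque scores over time (T_0_, T_1_, and T_2_) will be compared using the Friedman test". Normality is judged in the same section, where "interpreting the shape of the histogram and the Shapiro-Wilk test are used". The section does not say whether this applies to raw scores, paired differences or model residuals.

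For pain area under the curve, the same section gives a paired t test between sides, with the Wilcoxon signed-rank test as its non-normal replacement. The Abstract assigns paired parametric or nonparametric tests to the other outcomes, not to plaque.

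The intention-to-treat paragraph under Study Participants says that no participant is left out of the analysis and that the mixed model "handles missing data without formal imputation under the missing at random assumption".

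**The concern.** The Friedman test ranks related conditions within each participant and asks whether they differ. Here the named conditions are the three visits, and side of mouth does not enter. The rule therefore swaps a test of laceback against no laceback for a test of plaque over time.

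A time trend common to both sides is plausible. Interventions Common to Both Groups states: "Participants undergo one round of scaling before lacebacks are placed during T_0". The Introduction also argues that plaque builds up fastest while patients adapt to the appliance. The article gives neither the size nor the direction of any such trend.

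The P value for the primary outcome is at stake. A shared trend could give significance with no laceback effect, and a laceback effect that offsets a shared trend could be missed. The standard Friedman test also needs all three visits, so anyone missing T1 or T2 drops out, against the intention-to-treat commitment.

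**Working it through.** **1. Which contrast was the trial sized for?** Inputs from Sample Size Calculation: difference 1 OPI point, SD 1.88, alpha 0.05, power 85%, 34 participants, 10% dropout. Sidedness is not stated. Taking 1.88 as the SD of the within-participant difference and a two-sided paired t test, the noncentrality is (1/1.88) × √34 = 0.532 × 5.831 = 3.10 on 33 degrees of freedom. Power is 85.3%, and 34 is the smallest n that reaches 85%. Dropout: 34/0.9 = 37.8, so 38. The stated size reproduces as a paired between-side comparison, not as a test of change over visits.

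**2. Can the Friedman rule be read as a between-side test?**
- Run separately by side, it gives two within-side tests of time. Comparing their P values does not test the difference between sides.
- Run on the average of the two sides, it tests time alone.
- Run on all six side-by-visit cells, it mixes time with treatment.
- Run on the laceback-minus-control differences across visits, it would bear on treatment-by-time. The text does not say this.

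**3. Illustration.** Assumptions not in the article: 34 participants, participant SD 1, residual SD 1.88/√2 = 1.33 (so the between-side difference at a visit has SD 1.88), 4,000 simulated trials per row. Entries are the percentage with P<.05. Changes apply at T1 and T2.

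| Common change after T0 | Laceback effect | Friedman, laceback side | Friedman, control side | Friedman, two-side average | Friedman, six cells | Paired Wilcoxon at T2 |
|---|---|---|---|---|---|---|
| 0 | 0 | 5.5 | 4.8 | 5.8 | 4.8 | 5.0 |
| +1 | 0 | 76.2 | 75.8 | 96.7 | 94.5 | 5.0 |
| −1 | +1 | 4.8 | 75.4 | 44.7 | 95.0 | 82.8 |
| −0.5 | +1 | 25.4 | 23.8 | 4.9 | 86.8 | 83.2 |

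In row two the between-side null is true, yet every Friedman version rejects often. In row four a real 1-point effect gives 4.9% on the two-side average, against 83.2% for the paired test.

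A second set of assumptions (38 participants; participant, side and residual SDs 0.6, 0.3 and 0.4; common shift +0.5; no laceback effect) gave about 100% rejection per side. Those SDs imply a total SD of √(0.36 + 0.09 + 0.16) = 0.78, well below 1.88, so the range of 76% to 100% reflects the assumed SDs and shifts.

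**4. Would the fallback fire?** In simulated six-tooth OPI means, Shapiro-Wilk rejected in about 64% to 100% of trials on all 38 × 2 × 3 = 228 raw scores pooled. It rejected in about 4% to 40% in a single side-by-visit cell, and in 8% to 21% on T2 paired differences. The rate depends on the unit tested and the mean OPI, and the article fixes neither.

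**5. Missing visits.** With 38 recruited and 10% lost, about 0.10 × 38 = 3.8, or 4 participants, would lack a complete set of visits and leave a Friedman analysis.

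**The case against.** The strongest reply is that the defect is conditional. The mixed model is the stated plaque analysis and targets the right contrast, and the Abstract and the intention-to-treat paragraph name no fallback at all. The Friedman sentence also lacks the explicit word of replacement that the pain rule has, so it could be read as a supplement. This stands as a limit, although replacement is the natural reading of a rule that begins with a failed normality condition. The article also says that an intended analysis plan is available on the registry. That plan is not at hand and might name a paired test, but this would not correct the sentence printed here.

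A reader might infer that the fallback will almost certainly be used, because a bounded mean of tooth scores tends to fail Shapiro-Wilk. The documents do not support this. They specify no pooling of raw scores, they combine the test with a look at the histogram, and per-cell rejection can be low.

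A reader might also take rejection near 100% as the expected false-positive rate. That figure rests on SDs that the article does not give, and the exactly offsetting scenarios are constructed extremes. What survives does not need the simulations: the named test compares visits.

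**Conclusion.** The fallback is wrong as written. If it is used in place of the mixed model, the primary hypothesis is not tested and participants with a missed visit are lost. This follows from the wording and rests on no variance assumption. The rejection rates show direction only: about 76% to 100% per side under a common shift with no laceback effect, against 5% for a paired between-side test in the setting with SD 1.88. The probability that the rule is invoked is unknown.

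It does not follow that the plan as a whole leaves the primary hypothesis untested, since the mixed model tests it whenever the fallback is not invoked. The point still needs correcting before analysis, because the rule governs the primary outcome and a change made after seeing the data would look post hoc.

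**What to change.** Delete the Friedman sentence. Keep the mixed model as the primary analysis whatever the shape of the raw scores, and judge normality on its residuals. If the residuals are clearly non-normal, use a paired between-side method on each participant's laceback-minus-control difference in post-T0 OPI. The Wilcoxon signed-rank test already specified for pain would serve, as would a participant-clustered bootstrap confidence interval for the mixed-model contrast. State in advance which post-T0 visits form the difference, how a participant with only one of them is handled, and whether the T0 difference is adjusted for. Subtracting the T0 difference is optional and can cost power.

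The cost is a few sentences and no new data. If the fallback is used, a single-visit Wilcoxon test with 34 participants has about 84% power for a 1-point difference under normality (relative efficiency 3/π = 0.955; 36 needed for 85%). At the worst-case relative efficiency of 0.864, power is about 80% and 40 would be needed. With 24 of 38 enrolled, analysis due in October 2027 and the analyst kept blind to allocation, the change can still be made cleanly and dated.

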### Intervention

On one side that is randomly allocated, passive laceback is placed on the maxillary and mandibular arches prior to ligating the archwires. This is termed as “laceback side.” Laceback is not placed during the bond-up appointment, but 1 week after that (T_0_). Data collection for pain also commences after T_0_. This is to minimize the confounding effect of pain arising from initial archwire placement, which tends to subside in 1 week, as reported in the literature [31].

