#### Secondary Outcomes: Pain

Pain is recorded using the Visual Analog Scale, as it is the most widely used pain assessment scale and is suitable to be applied to the current age group of recruited participants. Pain score is recorded by the study participants on both laceback and no laceback sides. During T_0_, before placing lacebacks, the pain score is first recorded on both sides as baseline. Participants are given a pain diary to bring home during T_0_ and another copy during T_1_. At home, participants are reminded via mobile phone messaging (WhatsApp; Meta) to complete the pain diary. The pain diary given during T_0_ is collected back during T_1_ and T_2_. Participants are asked to rate the maximum pain experienced on each side during specific time points throughout the period between T_0_ and T_1_ and between T_1_ and T_2_. The time points are: 4 hours, 24 hours, 3 days, 1 week, 2 weeks, 3 weeks, 4 weeks from the review appointment. The 4-week time point can be recorded during the T_1_ or T_2_ appointment itself, or if the participant is unable to turn up for the appointments, they should record the pain score for the 4-week time point at home. Participants are instructed to place a mark along a 100-mm horizontal line at the most relevant position, whereby the left extreme indicates “no pain and discomfort” and the right extreme indicates “worst imaginable pain and discomfort.” Visual Analog Scale is measured to the nearest 1 mm using a standard metal ruler from the scale’s zero point to the patient’s mark and therefore quantified in a score with a range of 0 to 100. Each pain score reading is accompanied by an open-ended question asking what the cause of pain is (if any). Participants are informed that the pain recorded should arise from the laceback. Analgesics should not be taken prophylactically. If an analgesic is taken, the score should reflect the maximum pain experienced before taking the analgesic.

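### The pain AUC comparison makes no adjustment for the side-specific pain score recorded before laceback placement, and the article does not settle which pain analysis applies or how that score enters

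*Protocol article*

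**What the plan says.** Under Secondary Outcomes: Pain, the article collects a pre-placement score on each side: "During T_0_, before placing lacebacks, the pain score is first recorded on both sides as baseline". After that, "The time points are: 4 hours, 24 hours, 3 days, 1 week, 2 weeks, 3 weeks, 4 weeks from the review appointment", in each of the two four-week periods.

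Under Intended Statistical Analysis, "the pain scores are plotted against time to allow calculation of area under the curve (AUC) using the trapezoidal rule", and "Pain AUC will be calculated between T_0_ and T_1_ and T_1_ and T_2". The two values are then combined for each side: "The mean pain AUC for laceback and no laceback sides will be calculated by averaging pain AUC values". The comparison follows: "To compare differences in mean pain AUC of laceback and no laceback groups, a paired *t* test is used if data are normally distributed", with the Wilcoxon signed-rank test if normality fails. No change score, covariate or other baseline term appears. The Abstract agrees, giving the mixed model to plaque and paired tests to the other outcomes.

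The paragraph that follows the eligibility textbox under Study Participants says something different: "Repeated measures data for plaque score and pain score will be analyzed using a mixed model for repeated measures (MMRM". No terms are given there for pain. The only model spelled out under Intended Statistical Analysis is the one for plaque.

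Under Intervention, placement is put back to one week after bond-up: "This is to minimize the confounding effect of pain arising from initial archwire placement, which tends to subside in 1 week".

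**The concern.** A split-mouth comparison removes whatever a participant's two sides share, such as pain threshold, reporting style and general soreness. It does not remove a difference between the sides. One week after bond-up a participant may already be sorer on one side, for example from an ulcer over a bracket or wire end. The Introduction describes such lesions as common. If that soreness continues into the diary period, it is counted in that participant's laceback contrast.

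The score that could take it out is collected and named baseline, yet the specified test uses it only, if at all, as the first point of a four-week curve. The minimization factors are extraction pattern and side, not pain. The sample size was set on plaque alone, while the Discussion anticipates only a small pain increment. Avoidable noise therefore matters for this outcome.

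**Working it through.** **The plan's own figures.** The article gives no figure for pain. Its sample size for plaque reproduces: with SD 1.88 taken as the SD of the paired difference, the standardized effect is 1/1.88 = 0.532. A two-sided 5% paired t test then needs 34 pairs (power 85.3%), and 34/0.9 = 37.8, rounded up to 38. These are the pair counts used below.

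**Weight of the T0 score in the AUC.** Inputs are the pain time points in hours (0 for T0, then 4, 24, 72, 168, 336, 504, 672) and the trapezoidal rule. Each reading's weight is half the sum of its adjacent intervals.

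| Time (h) | Weight (h) | Share of first AUC |
|---|---|---|
| 0 (T0) | 2 | 0.30% |
| 4 | 12 | 1.8% |
| 24 | 34 | 5.1% |
| 72 | 72 | 10.7% |
| 168 | 132 | 19.6% |
| 336 | 168 | 25.0% |
| 504 | 168 | 25.0% |
| 672 | 84 | 12.5% |
| Sum | 672 | 100% |

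T0 has no place in the T1–T2 curve, so its share of the averaged AUC is 0.298%/2 = 0.149%. If the curve is built only from take-home diary entries, the share is zero.

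**What that means for a side difference.** Take an illustrative 10 mm difference.
- Present at T0 only: it moves the time-averaged pain difference by 10 × 0.00298 = 0.03 mm in the first period and 0.015 mm in the two-period mean.
- Persisting unchanged to 24 hours: (2 + 12 + 34)/672 = 7.1% of the first AUC is affected.
- Persisting to one week: 252/672 = 37.5%.
- Persisting to four weeks: 100%.

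Only persistence matters, and the documents give no figure for it.

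**Validity of the unadjusted test.** Simulating 34 pairs with randomized side and a T0 difference correlated 0, 0.5 or 0.7 with the outcome difference gave type I error between 4.8% and 5.2%. The test holds its level.

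**Chance imbalance.** With 34 pairs, the mean T0 side difference has a 95% range of ±1.96 × SD/√34. For an assumed SD of 5, 10 or 20 mm this is ±1.7, ±3.4 or ±6.7 mm. Only the part that persists reaches the AUC contrast.

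**Gain from adjustment.** Let r be the correlation between the T0 side difference and the AUC side difference. Regressing the second on the first multiplies the variance by 1 − r². Estimating the slope costs an expected factor (n − 2)/(n − 3) under normality, which is 36/35 = 1.029 at n = 38.

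| Assumed r | 1 − r² | × 36/35 | SE factor |
|---|---|---|---|
| 0 | 1.00 | 1.03 | 1.01 |
| 0.1 | 0.99 | 1.02 | 1.01 |
| 0.3 | 0.91 | 0.94 | 0.97 |
| 0.5 | 0.75 | 0.77 | 0.88 |
| 0.7 | 0.51 | 0.52 | 0.72 |

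Break-even is where 1 − r² = 35/36, so r = 1/6, about 0.17. With 34 pairs the slope cost is 32/31 = 1.032, which changes little.

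Plain subtraction of baseline is not a safe alternative. With equal SDs its variance factor is 2 − 2r, so it helps only if r exceeds 0.5.

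**The case against.** The strongest reply is that nothing in the specified test is wrong. Side is randomized, an unadjusted paired comparison of a secondary outcome is conventional, and a measure of pain after placement ought to give a pre-placement reading little weight. All of that stands. A reader might infer from the 0.30% weight, or from the missing baseline term, that the laceback estimate is biased. The documents do not support that: randomization gives pre-existing side differences an expectation of zero in the contrast.

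A reader might also infer that the T0 score goes unused. That is too strong as well. The mixed model named for pain scores could include T0, as the plaque analysis includes its own T0 measurement, and baseline characteristics are to be described. But no terms are given for pain, so naming the model does not settle whether or how T0 enters.

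The design also limits the problem. Placement is delayed by a week, extractions come at least two weeks before bond-up, participants are taught to localize pain and are asked its cause, and they are told to record pain from the laceback. This makes low values of r plausible. If most T0 scores are near zero, a few participants could dominate the slope. Both points stand, so the gain may be small or slightly negative and the analysis needs a fallback.

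Finally, adjustment might be left to the separate analysis plan, which is not shown. That reply is weaker here, because the article itself states the pain test and its non-parametric alternative and, in another place, a different method.

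**Conclusion.** The concern holds in a limited form. The specified AUC comparison does not adjust for the side-specific pre-placement score, whose weight is at most 0.30% of the first AUC and 0.15% of the average. The article also names two methods for pain without saying how they relate. The consequence is possible loss of precision and uncorrected chance imbalance in a valid test.

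The size rests on the assumed r. At 38 pairs, adjustment gives a variance cut of about 6% at r = 0.3, 23% at 0.5 and 48% at 0.7. Below r of about 0.17 there is a small loss, at most about 3%. These figures also assume roughly normal differences and no dominating T0 values. The possible gain is larger than the possible loss and the data are already being collected, so the change is worth making, but the trial's validity does not depend on it.

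**What to change.** - **Reconcile the two statements.** Study Participants and Intended Statistical Analysis should name the same main pain analysis. If a mixed model for pain is kept in any role, give its terms and say whether T0 is an outcome level or a covariate.
- **Prespecify the adjusted comparison before unblinding.** Regress each participant's mean AUC difference (laceback minus no laceback) on the T0 pain difference taken the same way round. The intercept, at zero T0 difference, is the laceback effect.
- **Keep a route for awkward data.** Use a robust, rank-based or permutation version if residuals are non-normal or a few T0 differences dominate.
- **Retain the unadjusted paired t or Wilcoxon test** as a sensitivity analysis.
- **Use the T0 score as recorded.** With 24 participants enrolled and 14 complete at submission, its definition should not be changed mid-trial.

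The cost is a few sentences of analysis text, one degree of freedom and the worst-case precision loss given above. No new data, visits or participants are needed. The primary analysis is scheduled for October 2027 and allocation codes are withheld from the analyst until the major analyses are done, so there is still time to fix this in advance.
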